### Study phase 2: testing of initial Hub theory using empirical data

We will empirically test the initial programme theory for the Hubs through a mixed-methods process with 6 and 12 months outcomes evaluation. The evaluation aims to assess for whom, how and why the Hub models had an impact (if any) in the two different contexts of Wyndham Vale and Marrickville across the child, caregiver, practitioner and system level outcomes specified in figures 2 and 3, table 1 and ‘Outcomes Assessment’ below.

**Table 1 T1:** Primary and secondary outcomes

Primary outcomes		Baseline assessment		6 and 12 months post Hub implementation begins	
		**Caregiver survey**	**Practitioner survey**	**Caregiver survey**	**Practitioner survey**
*Caregiver*					
Identification of adversity	Increase in the proportion of caregivers who report being asked by a service provider about adversity in the past 6 months.	X		X	
Intervention for adversity	Increase in the proportion of caregivers who report spending extra time with or receiving an intervention from a Hub service provider for adversity in the past 6 months.	X		X	
Referrals for adversity	Increase in the proportion of caregivers who report receiving a referral to an intersectoral service for adversity in the past 6 months.	X		X	

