### Outcome evaluation

#### Design

The study is a mixed-methods repeated measures evaluation that uses caregiver and Hub practitioner surveys at baseline, 6 and 12 months after Hub implementation begins and in-depth interviews at 12 months.

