##### Caregivers

Potential caregiver participants are those who: (i) care for a child aged 0–8 years, including women who are pregnant, (ii) access any of the universal or specialist services provided in the Hub, such as general practitioners (GPs), paediatricians, lawyers and (iii) can understand written or spoken English language. The English language criterion is a limitation of our study; however, funding is not available to provide interpreters. Furthermore, culturally and linguistically diverse persons participated in an informed and meaningful way in phone-based or in-person surveys for HHAN (personal communication [name]).

Given the preventative focus of this study, caregivers will not be screened for adverse experiences as an inclusion criterion. Instead, caregivers will report the frequency of 15 adversity types in the baseline survey. These adversity types are derived from the Parent Engagement Resource^61^ and include challenges with: social support, finances, housing, employment, family physical health, parent mental health, parenting, child neglect, alcohol and substance use, family relationships, family violence, child abuse, visa and immigration issues, crime issues and discrimination.

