#### Data collection

##### Caregiver and Hub practitioner surveys

The Caregiver and Hub practitioner baseline and outcome surveys consisting of the measures outlined in table 1 and available in online supplemental file 1 will be built in Research Electronic Data Capture (REDCap)^63^ hosted by Murdoch Children’s Research Institute. After completing an informed consent process, caregivers can complete the baseline survey: (i) in paper form, (ii) over the telephone with a researcher or (iii) online. Practitioners will complete the practitioner baseline survey in paper form or online via REDCap. The practitioner survey will be sent towards the end of baseline data collection to minimise the potential impact of the survey on clinical practice prior to the Hub testing period. Caregiver and practitioner participants will be contacted by telephone, email or text message by the research team 6 and 12 months after the Hub implementation begins and invited to complete the follow-up survey.

10.1136/bmjopen-2021-055431.supp1Supplementary data

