#### Quantitative data analysis

Statistical analyses will be conducted using Stata or R statistical software packages.^65 66^ The baseline characteristics of the caregivers, children and practitioners will be described using the mean, median and IQR for continuous data and proportions for categorical data. Primary and secondary outcomes will be assessed by examining change in proportions/means from baseline to 6 months, from 6 to 12 months and from baseline to 12 months. We will also conduct linear regression analyses to assess the association between each caregiver-reported primary outcome at 6 and 12 months with the outcomes of child and caregiver mental health and caregiver quality of life, at 6 and 12 months, respectively.

Quantitative measures of the strength and structure of service linkages between Hub practitioners will be analysed using social network analysis (SNA) software package UCINET.^67^ SNA is a complex systems discipline and quantitative methodology widely used to measure networked relationships between organisations and individual actors in health service and policy settings.^68–71^ UCINET^67^ will calculate indicators (ie, density, degree, centrality and betweenness) for the network and each Hub practitioner based on: (i) contact, (ii) referrals to and from and (iii) quality of the relationship. These indicators and analytical approach are recommended for descriptive social network analysis.^68–71^

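### Primary outcomes (ii) intervention and (iii) referral are scored over all caregivers, so each proportion mixes how many families have an adversity with how well the Hub responds to it

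*Protocol article*

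**What the plan says.** Table 1, in the Study phase 2 section, words the referral outcome as "Increase in the proportion of caregivers who report receiving a referral to an intersectoral service for adversity in the past 6 months". The intervention outcome is likewise the "proportion of caregivers who report spending extra time with or receiving an intervention from a Hub service provider for adversity". Neither is limited to caregivers who have an adversity.

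The Caregivers section says that "caregivers will not be screened for adverse experiences as an inclusion criterion", and gives the study's preventative focus as the reason. In place of screening, "caregivers will report the frequency of 15 adversity types in the baseline survey".

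The Quantitative data analysis section assesses the outcomes by "examining change in proportions/means from baseline to 6 months, from 6 to 12 months and from baseline to 12 months". It mentions no restriction to, or adjustment for, families with a need. The Design section describes a "repeated measures evaluation that uses caregiver and Hub practitioner surveys at baseline, 6 and 12 months after Hub implementation begins", so enrolled caregivers are followed over time, and there is no comparator.

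On survey content, the surveys section refers to the "measures outlined in table 1 and available in online supplemental file 1". That supplement is not among the documents at hand.

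**The concern.** Outcome (i), being asked about adversity, can apply to every caregiver. Outcomes (ii) and (iii) are different: an intervention or referral for adversity is a success only where there is an adversity to respond to. Over all caregivers, a no can mean that nothing was needed or that a need went unanswered, and the proportion cannot tell these apart.

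The study's aim is detection of and response to adversity. The change in (ii) and (iii) would be read as a change in response, but it also carries any change in how many families have a need. The plan gives reasons to expect need to move. Caregivers are recruited in waiting rooms or through practitioners, so at a point of service contact. The logic model expects caregiver mental health to improve, and parent mental health is one of the 15 listed adversities. A Hub that relieved need could therefore lower the very proportions that Table 1 expects to rise. Without a comparator, nothing in the design removes such a shift.

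**Working it through.** The article gives no expected proportions, effect size or power for these outcomes, so there is no stated figure to reproduce. Every rate below is an assumption chosen to show direction and size.

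**Set-up.** Let *p* be the share of caregivers with an adversity in the 6-month window (need), and *r* the share of those who report an intervention or referral for it (response). Assume that nobody without an adversity reports one. The Table 1 proportion is then

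P = p × r,

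and its change between two surveys splits exactly into

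P₁ − P₀ = p₀(r₁ − r₀) + r₁(p₁ − p₀).

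The first term is the response and the second is the shift in need. P cannot exceed p.

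**Stable need: dilution only.** If p₁ = p₀, the second term is zero. A 20-point gain in response (30% to 50%) then shows as:

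| Need | Whole-sample change | Change among those with need |
|---|---|---|
| 30% | 0.3 × 20 = 6 points | 20 points |
| 50% | 0.5 × 20 = 10 points | 20 points |
| 70% | 0.7 × 20 = 14 points | 20 points |

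**Shifting need: hidden or mimicked change.**

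| Need | Response | Whole-sample proportion | Change |
|---|---|---|---|
| 50% to 40% | 40% to 50% | 0.5 × 0.4 = 20% to 0.4 × 0.5 = 20% | 0 |
| 50% to 30% | 30% to 50% | 0.5 × 0.3 = 15% to 0.3 × 0.5 = 15% | 0 |
| 50% to 60% | 40%, unchanged | 0.5 × 0.4 = 20% to 0.6 × 0.4 = 24% | +4 points |
| 40% to 60% | 30%, unchanged | 0.4 × 0.3 = 12% to 0.6 × 0.3 = 18% | +6 points |

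In the first row the split is 0.5 × 0.10 = +0.05 from response and 0.5 × (−0.10) = −0.05 from need, which cancel. In the third it is 0 from response and 0.4 × 0.10 = +0.04 from need.

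**Does a smaller denominator cost precision?** Take 200 caregivers per survey (the lower end of the planned 200–400), need constant, response 30% to 50%, and treat the surveys as unpaired. Restriction leaves 60, 100 or 140 caregivers at need of 30%, 50% or 70%. Approximate power is 46%, 71% and 88% over all caregivers, against 61%, 83% and 93% among those with need. In this illustration the undiluted difference more than repays the lost numbers. The figures ignore pairing and dropout and serve only for comparison.

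**Is need measured at follow-up?** The Caregivers section places the 15-type list in the baseline survey and says nothing about 6 or 12 months. Table 1 has no row for adversity frequency at any time point, baseline included, although the list is in the baseline survey. Table 1 is therefore not a complete inventory, and its silence settles nothing about follow-up.

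**The case against.** The strongest defence is that the denominator is a reasoned choice. The Hub is preventative and open to every entrant, and the share of all users who receive a response is a legitimate measure of reach. That stands, and it is why the whole-sample figure should stay.

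Second, restriction has its own bias. Hub practitioners are trained to open conversations about adversity, so caregivers may recognise and report more of it after implementation. A same-window denominator could then be altered by the intervention and would compare different people at each survey. That also stands, and argues against making it the sole main estimate.

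Third, restricted analyses are often left to an analysis plan, and the article already concedes that change cannot be attributed directly to the Hub. This carries less weight. The denominator is set by the outcome definition itself, and the concession about attribution does not address a mixture that data on need could separate. The health economics section does distinguish met need, unmet need and no need, but through child questionnaires rather than the 15 family adversities.

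Some stronger readings are tempting but unsupported:

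- A reader might infer that adversity is recorded only at baseline. The article neither says nor excludes this, and the survey supplement is not shown.
- A reader might infer that the proportions track need instead of response. They track both; with stable need, a rise does reflect more response.
- A reader might infer that recruiting many low-need families could create a change. In a repeated-measures sample it scales the change but cannot produce or reverse one. That takes a shift in need within families, or selective dropout.
- A reader might infer that the question of for whom the Hub works cannot be answered. Baseline adversity allows a partial answer.

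**Conclusion.** The point holds in a limited form. As defined and analysed in the article, outcomes (ii) and (iii) combine prevalence of need with response to need, and no stated analysis separates them. With stable need, the consequence is an understated effect: 6 to 14 points in place of 20 for need between 30% and 70%. With need moving by 10 points, a 10-point gain in response can vanish, or a 4-point rise can appear with no better response.

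These sizes rest on assumed rates and on the assumption that caregivers without an adversity report no intervention or referral for one. How far need will actually move is unknown. If nearly all caregivers report at least one of the 15 broad adversity types, dilution is slight. Outcome (i) is properly scored over all caregivers. Severity is minor to moderate: the outcomes remain usable, but their change cannot be read as change in response without need beside it.

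**What to change.** 1. State whether the 15-type adversity list is asked at 6 and 12 months. If not, add it, with a 6-month recall period to match the outcomes.
2. Keep the whole-sample proportions for (ii) and (iii), labelled as reach.
3. Pre-specify (ii) and (iii) in two further sets: the fixed set reporting at least one adversity at baseline, for which the data are already planned, and those reporting at least one adversity in the same 6-month window.
4. Show the prevalence of need at each survey beside these estimates.
5. Leave (i) over all caregivers.

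The cost is smaller denominators for the restricted estimates and, if the list is not already repeated, about 15 more items in two surveys. Neither restricted set is clean: need in the baseline set may fall over time, and the same-window set may be changed by the Hub's effect on recognising adversity. The two should be read together, and neither should replace the whole-sample figure.

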**Secondary outcomes**					
*Child*					
Infant temperament	Increase in the proportion of caregivers who report their infant is easier/much easier than average; assessed through single caregiver-reported item on infant temperament; has a moderate correlation (*r*=0.51) with the Easy-Difficult Scale (EDS) of Australian version short form of Revised Infant Temperament Questionnaire^78^; completed for one child* aged 0–8 in each family 0 to <2 years.	X		X	
Child mental health	Decrease in the mean scores for caregiver-reported internalising or externalising symptoms for their child. Completed for one child* in each family. For children aged 0 to <2 years: Ages & Stages Questionnaire Social-Emotional Second Edition (ASQ-SE2).^79^† For children aged ≥2 to 8 years: Strengths & Difficulties Questionnaire.^80^	X		X	
Global health	Increase in the mean scores of caregiver-reported general child health; assessed through single item (GHQ-S1) from Child Health Questionnaire^81^; completed for one child* aged 0–8 in each family.	X		X	
*Caregiver*					
Uptake of referrals	Increase in the proportion of caregivers who report uptake of referrals to other services in the past 6 months.	X		X	
Mental health	Decrease in the mean scores of caregiver-reported psychological distress as assessed by Kessler Psychological Distress Scale 6 (K6); 6-item.^82^	X		X	
Global health	Increase in means scores of caregiver-reported general health; assessed through single item of the Short Form Health Survey (SF-12).^83^	X		X	
Parental warmth, parenting hostility and efficacy	Increase in mean scores of parental warmth and efficacy; decrease in mean scores on parenting hostility. Three self-report subscales drawn from the Longitudinal Study of Australian Children (LSAC), Australia’s first nationally representative longitudinal study of child development which will allow for national comparisons of the study data^84^; assessing parental warmth, parenting hostility and efficacy. Parental warmth (6-items), parenting hostility (5-items) and parenting efficacy (4-items).	X		X	
Quality of life	Increase in mean caregiver quality of life scores calculated from the EuroQol Health and Well-being Instrument Short Form (EQ-HWB-S).^72^	X		X	
Caregiver experience	Caregiver reported acceptability and feasibility of the Hub; Increase in the proportion of caregivers who report their satisfaction with Hub care as measured by three items from the Australia Bureau of Statistics Patient Experiences in Australia Survey.^85^	X		X	
Personal well-being	Increase in mean scores of caregiver-reported personal well-being outcomes measured by the Personal Well-being Index; 7 items.^86^	X		X	
*Practitioner*					
Identification of adversity	Increase in the proportion of practitioners who report asking about adversity in the past 6 months.		X		X
Intervention for adversity	Increase in the proportion of practitioners who report spending extra time or providing an intervention for adversity in the past 6 months.		X		X
Referrals for adversity	Increase in the proportion of practitioners who report referring caregivers to an intersectoral service for adversity in the past 6 months.		X		X
Practitioner experience	Practitioner reported acceptability and feasibility of the Hub; Increase in the proportion of practitioners who report feeling confident and competent to detect and support families experiencing adversity.		X		X
*System level*					
Strength and structure of intersectoral service linkages	Increase in the number and strength of service linkages between Hub practitioners as assessed through social network analysis (SNA) indicators for network density, degree, centrality and betweenness, and map of linkages between Hub practitioners based on i) contact, (ii) referrals to, (iii) referrals from, and (iv) quality of the relationship.^68–71^		X		X
Health economics outcomes	Costs of implementation of the Hub models, caregiver-reported intersectoral service usage and value of unmet need.	X		X	

*Caregivers with more than one child will respond to questions pertaining to one child in their family based on the child they are most concerned about.

†The ASQ-SE is limited by its design as a screening tool that may not be a sensitive outcome measure. The measure is used in this study because it more directly measures mental health and well-being than the ASQ.

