##### Secondary outcomes

1.2. Hub practitioner-reported (i) identification of, (ii) interventions delivered and/or (iii) referrals provided for adversity,1.3. Caregiver-reported uptake of referrals,1.4. Child and caregiver mental health,1.5. Infant temperament,1.6. Child and caregiver global health,1.7. Caregiver parenting,1.8. Caregiver quality of life,1.9. Caregiver personal well-being outcomes,1.10. Caregiver experience of care,1.11. Practitioner experience including confidence and competence in detecting and responding to adversity,1.12. Linkages between intersectoral Hub practitioners, and

2. To determine the costs of implementing the Hub models, and

3. To determine the extent that the Hub models are providing the intended service option (ie, acceptability, feasibility and fidelity to the initial Hub programme theory).

Reporting in this protocol is based on the Strengthening the Reporting of Observational Studies in Epidemiology (STROBE) Statement.^35^

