#### Participants

We aim to recruit two stakeholder groups: caregivers (n*=*100–200 per site) and Hub practitioners (n=20–30 per site).

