##### Hub practitioners

Potential practitioner participants are those who: (i) work in any of the intersectoral services provided as part of each Hub, including GPs, maternal and child health nurses, paediatricians, allied health professionals, social workers, lawyers, and (ii) can understand written or spoken English language.

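### The outcome labelled intersectoral service linkages is measured by network indicators that, as stated, do not separate ties across services or sectors from ties within one service

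*Protocol article*

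**What the plan says.** The system-level part of Table 1 in the protocol article names the outcome "Strength and structure of intersectoral service linkages". The definition beside that name is "Increase in the number and strength of service linkages between Hub practitioners as assessed through social network analysis (SNA) indicators for network density", followed by degree, centrality, betweenness and a map of linkages. The intended direction is an increase.

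Under Quantitative data analysis, the network software "will calculate indicators (ie, density, degree, centrality and betweenness) for the network and each Hub practitioner". The ties are "i) contact, (ii) referrals to and from and (iii) quality of the relationship". Neither place limits ties to pairs from different services or sectors, and neither lists an indicator split by service or sector.

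Objective 1.12 words the outcome as "Linkages between intersectoral Hub practitioners". The Hub practitioners section makes eligible those who "work in any of the intersectoral services provided as part of each Hub, including GPs, maternal and child health nurses, paediatricians, allied health professionals", and also social workers and lawyers. The Participants section aims for 20 to 30 practitioners per site. The survey items that generate the ties are in online supplemental file 1, which is not shown.

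**The concern.** The row name attaches the word intersectoral to the linkages; the definition and the indicators do not. The same table does apply such a limit elsewhere: its referral rows, for caregivers and for practitioners, require that the referral go to an intersectoral service. In the network row the word appears in the name only.

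With 20 to 30 practitioners drawn from any Hub service, several will probably share a service. A tie between two nurses then counts in density and degree exactly as a tie between a nurse and a lawyer does. The Introduction gives siloed service systems as the problem to be solved, so a reader will take a rise in this outcome as evidence that the silos have been bridged. If the rise came from closer contact among colleagues in one service, that conclusion would not follow from the figure reported.

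**Working it through.** The protocol gives no figure for this outcome, so there is none to reproduce. The check is whether the stated indicators can rise while links between groups stay the same.

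**Inputs.** From the protocol: 20 to 30 practitioners per site. Assumed: the number and size of the groups, and the tie densities. A group may be a service or a sector; the arithmetic is the same.

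**Formulas.** With n practitioners there are T = n(n − 1)/2 pairs, of which W are within a group and C = T − W are between groups. If w and c are the tie densities in the two kinds of pair:

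- overall density D = (W·w + C·c)/T
- mean degree = D·(n − 1)

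For directed ties such as referrals, all pair counts double and the densities are unchanged.

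**Main illustration: 25 practitioners, 5 groups of 5.** T = 25 × 24/2 = 300, W = 5 × 10 = 50, C = 250. Let w rise from 0.5 to 0.9 and keep c at 0.10.

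- Before: (50 × 0.5 + 250 × 0.10)/300 = 50/300 = 0.167; mean degree 0.167 × 24 = 4.0.
- After: (50 × 0.9 + 250 × 0.10)/300 = 70/300 = 0.233; mean degree 0.233 × 24 = 5.6.
- Relative rise: 70/50 = 1.40, or +40%.
- Between-group mean degree: 2 × 250 × 0.10/25 = 2.0 at both times.

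**Other layouts, same change in w, c still 0.10.**

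| Layout (assumed) | W of T | D before | D after | Relative rise |
|---|---|---|---|---|
| n = 20, 4 groups of 5 | 40 of 190 | 35/190 = 0.184 | 51/190 = 0.268 | +46% |
| n = 30, 5 groups of 6 | 75 of 435 | 73.5/435 = 0.169 | 103.5/435 = 0.238 | +41% |
| n = 25, groups of 10, 10 and 5 | 100 of 300 | 70/300 = 0.233 | 110/300 = 0.367 | +57% |

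**Sensitivity in the other direction (25 practitioners, 5 groups of 5).**

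- If same-group colleagues are already well connected, so that w moves only from 0.9 to 1.0, D goes from 70/300 = 0.233 to 75/300 = 0.250, or +7%.
- A between-group rise of 0.10 adds 250 × 0.10/300 = 0.083 to D. The within-group jump of 0.40 adds 50 × 0.40/300 = 0.067.

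**Opposite movement.** This needs within-group and between-group densities to move in opposite directions. With w from 0.40 to 0.90 and c from 0.15 to 0.10, D goes from (20 + 37.5)/300 = 0.192 to (45 + 25)/300 = 0.233 while between-group ties fall by a third.

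**Betweenness.** In 300 simulated networks per setting (25 practitioners, 5 groups of 5), mean betweenness fell from 14.4 to 8.9 when only between-group density rose, from 0.15 to 0.30, with w at 0.40. Mean betweenness therefore does not supply the missing split: in this setting it went down as between-group links increased.

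**The case against.** **The plan does not say that all ties count.** This is right. It is inferred from indicators defined for the network and each practitioner, with no restriction stated. If the survey items ask only about contacts and referrals with other services, same-service ties never enter the data and the service-level concern goes. This condition stays in the conclusion.

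**Objective 1.12 is consistent with the measure.** This also stands. The objective applies intersectoral to the practitioners, and so do other parts of the article. A reader might infer that the measure contradicts the objective; it does not. The mismatch lies between the Table 1 row name and the definition beside it.

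**Referral ties probably run mainly between services.** This is plausible, and the planned workforce discussions aim at warm referrals between practitioners of different sectors. The concern is strongest for contact and relationship quality. That is a reason to report by tie type.

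**The size is assumed, and most pairs are between groups.** This is true: in the equal-group layouts 79% to 84% of pairs are between groups (150/190 at the lower end, 160/190 for 5 groups of 4 at the upper), so density reflects them more than within-group pairs. Nothing in the article suggests that co-location would mainly strengthen ties within a service. The illustration shows what the indicator cannot exclude, not what is expected.

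**A sector-only headline would lose ties that matter.** This is a fair warning. A GP and a maternal and child health nurse work in different services but arguably in one sector. Counting only between-sector pairs could drop links that the Hub also means to build, so both levels are needed.

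**This is analysis-plan detail, and other data are triangulated.** This is only partly so. A breakdown by practitioner attribute could be left to an analysis plan, and interviews and process data will help interpretation. But the outcome name, its definition, the direction of benefit and the indicators are all set in this article, and name and definition do not match.

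**Conclusion.** The point holds in a conditional form. As stated, the indicators cannot tell ties between services or sectors from ties within one service, yet the outcome carries an intersectoral label. Unless the survey items restrict ties to other services, a within-service rise could be reported as better intersectoral linkage. In the layouts above, a within-group rise from 0.5 to 0.9 with no between-group change raises overall density by 40% to 57%. The rise is only 7% if colleagues start at 0.9 (25 practitioners, 5 groups of 5). All these figures rest on assumed group sizes and densities.

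A reader might go further and infer that the outcome will move opposite to cross-sector integration. The documents do not support that. It is arithmetically possible, but only if the two kinds of tie move in opposite directions, and nothing in the article indicates that they would.

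The outcome is secondary and its analysis descriptive. What is affected is the interpretation of the network result, not the primary outcomes.

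**What to change.** Record each practitioner's service and sector as node attributes. For each tie type and each wave, report density and mean degree for between-service pairs and for between-sector pairs, with the within-group values beside them. Base any statement about intersectoral linkage on the between-group figures, and keep the whole-network and per-practitioner indicators as descriptive. State in Table 1 whether the survey items cover ties within a practitioner's own service.

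The cost is one further summary of the same tie data, with no new participants. The drawback is fewer pairs behind the between-group figures: in the illustration, 250 rather than 300, and fewer where groups are large or unequal (200 of 300 with groups of 10, 10 and 5).
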